## Abstract

**Background:**

About 15% of patients fail to achieve a satisfactory clinical outcome following knee replacement, which may indicate the existing model of rehabilitation after surgery is possibly not the most efficacious. The COmmunity-based Rehabilitation after Knee Arthroplasty (CORKA) trial evaluates the effects of a new multi-component community-based rehabilitation programme following knee replacement compared with usual care.

**Methods/design:**

The CORKA trial is a multi-centre, single-blind, two-arm randomised controlled trial. The primary outcome is the Late Life Function and Disability Instrument (LLFDI) overall function score measured at 12 months post-randomisation which will be analysed using a linear mixed effects model. Secondary outcomes are measured at 6 and 12 months post-randomisation and include the LLFDI frequency and limitation total dimension scores, the Oxford Knee Score, the Knee injury and Osteoarthritis Outcome Score quality of life subscale, the Physical Activity Scale for the Elderly, the EuroQol EQ-5D-5L, and several measurements of physical function*.* Full details of the planned analysis approaches for the primary and secondary outcomes are described here, as are the descriptive statistics which will be reported. This is an update to the CORKA protocol which has already been published in this journal.

**Discussion:**

This paper provides details of the planned statistical analyses for this trial and will reduce the risks of outcome reporting bias and data-driven results.

**Trial registration:**

ISRCTN registry, 13517704. Registered on 12 February 2015.

## Background

Osteoarthritis is the most common cause of disability in older people [1], with painful knee osteoarthritis affecting 10% of people older than 55 in the UK [2]. The number of knee replacements taking place in the UK has risen significantly in recent years; in 2016, 98,147 primary knee replacements were recorded [3]. Outcomes following knee replacement are known to be multi-faceted; around 15% of patients do not report a good outcome from their knee replacement and have continuing pain and mobility problems [4]. Factors such as the amount of pain and limitation of balance and muscle strength may contribute to poorer outcomes [5].

Best practice guidance from the UK and North America recommends that a multi-disciplinary approach to rehabilitation improves outcomes [6–8]; it is believed that such an approach may contribute to optimising post-operative return to functional activity. In addition, it is clear from existing studies that current rehabilitation strategies do not meet the needs of all patients, particularly those who are socially isolated; do not have easy access to transport; or who are frail. A review examining multi-disciplinary rehabilitation programmes following hip and knee joint arthroplasty indicated that home-based care may be beneficial; however, it concluded that further high-quality research is needed [8].

The COmmunity-based Rehabilitation after Knee Arthroplasty (CORKA) trial is a multi-centre, single-blind, two-arm, randomised controlled trial designed to compare the clinical outcomes of a new home-based multi-disciplinary rehabilitation protocol with usual care in patients assessed pre-operatively as being at risk of a poor outcome. The protocol paper for the CORKA trial has been published previously [9]; the aim of this paper is to report in detail the analysis plan as agreed on by the trial steering committee in October 2017.

## Methods/design

### Trial design

CORKA is a multi-centre, single-blind, two-arm, individually randomised controlled, superiority trial with blinded outcome assessment at 6 and 12 months post-randomisation. Randomisation uses a 1:1 ratio, is stratified by study centre, and is performed via a secure, web-based randomisation system. The nature of the intervention means participants and those delivering the intervention are not blinded to treatment allocation; however, clinical outcome assessors remain blinded to treatment allocation where possible. Eligible participants identified pre-operatively as being at risk of a poor outcome using the study screening tool [10] are randomised to receive either a new multi-component community-based rehabilitation programme or usual care. Outcomes are assessed at baseline and at 6 and 12 months post-randomisation. Full details of the trial design, study population, and study procedures have been published previously [9].

The trial is registered with the International Standard Randomised Controlled Trials database, ISRCTN reference number 13517704.

### Objectives

The primary objective of this study is to determine if a multi-component rehabilitation programme improves the outcome at 12 months after surgery of patients who undergo knee replacement. The null hypothesis is that there is no difference in patients’ functional abilities between the two treatment groups. Secondary objectives include assessing the impact of the rehabilitation programme on physical function and quality of life at 6 and 12 months after randomisation, and a cost effectiveness analysis of the new therapy versus usual care rehabilitation up to 12 months after randomisation.

### Outcomes

#### Primary outcome

The primary outcome is the Late Life Function and Disability Instrument (LLFDI) overall function score [11] measured at 12 months post-randomisation. The LLFDI overall function score consists of 32 items, and scores range from 0 to 100 with higher scores indicating better functionality. The LLFDI overall function score is also measured at 6 months post-randomisation.

#### Secondary outcomes

The secondary outcome measures, recorded at 6 and 12 months post-randomisation, are as follows:LLFDI frequency and limitation total dimension scores: 16-item patient reported outcome measures (PROMs), each with a total score ranging from 0 to 100, with higher scores indicating higher levels of frequency of participation in life tasks and capability of participation in life tasks respectively.The Oxford Knee Score (OKS) [12]: a 12-item PROM with total scores ranging from 0 (most severe symptoms) to 48 (least severe symptoms).The Knee injury and Osteoarthritis Outcome Score (KOOS) quality of life subscale [13]: four self-reported questions with total scores ranging from 0 (extreme problems) to 100 (no problems)The Physical Activity Scale for the Elderly (PASE) questionnaire [14]: a 12-item, self-reported measure. The time spent participating in each activity is multiplied by a weight corresponding to that activity, and these weighted values are summed to calculate total PASE scores, with higher scores indicating greater levels of physical activity.Health economics using the EuroQol EQ-5D-5L [15]: a self-reported outcome measure consisting of 5 dimensions each with 5 possible responses which are converted to multi-attribute utility scores, where 1 represents perfect health, 0 represents death, and scores less than 0, representing a quality of life worse than death, are possible.Measurement of physical function using the 30-s chair stand test, the figure of 8 walking test, and the single-leg stance test.

For the subgroup of patients who reach 2 years post-randomisation prior to the end of the trial, questionnaire data will be collected at this time point. This will include the LLFDI overall function score, and frequency and limitation total dimension scores, the OKS, the KOOS quality of life subscale, the PASE, and the EuroQol EQ-5D-5 L.

#### Safety outcomes

The number of adverse events and serious adverse events occurring whilst a participant is continuing in the study up to 12 months post-randomisation will be reported along with the relatedness of these events to the treatment. Serious adverse events are defined as those that are fatal, life threatening, or disabling, or that require hospitalisation or prolongation of hospitalisation.

### Sample size

The primary outcome in the CORKA trial is the LLFDI overall function score at 12 months. No existing information was available about the minimum clinically important difference for this scale; however, it was believed to be the most clinically relevant outcome in this population. Therefore, the sample size calculation was based on a moderately small standardised effect size of 0.275. This standardised effect size is, for example, equivalent to detecting a 3-point difference between treatment arms on the LLFDI overall function score assuming a standard deviation of 10.91 and no clustering effect across centres [16]. Six hundred and twenty participants (310 per arm) are required to detect a standardised effect size of 0.275 with 90% power, 5% (two-sided) significance, and allowing for 10% loss to follow-up based on previous experience of trials in a similar population.

An internal pilot study was conducted at one site (Oxford) to review for recruitment feasibility and to confirm the intervention package. Fifteen patients were randomised during this pilot study, and these patients will be used in the final analysis, since the intervention package was not changed between the pilot and the main trial.

### Statistical analysis

#### General analysis principles

Two analysis populations will be considered: (1) the intention-to-treat (ITT) population; and, (2) the per-protocol (PP) population. The ITT population will include all randomised participants analysed according to the intervention to which they were randomised. The ITT population will be the primary analysis set, and all analyses will be conducted for this population if not otherwise stated. Analyses on this population provide an estimate of the effect of treatment offer.

The PP population will be analysed according to the intervention they actually received. Participants with major protocol deviations or violations, that is, those who did not receive treatment or did not provide any follow-up data, will be excluded from the PP population. The definition of the PP population will be finalised by the trial statistician during a blinded analysis of the data (i.e. without details of treatment allocation) prior to the primary analysis time point; any unanticipated protocol deviations which occur will be identified at this point. Analysis of the PP population will be conducted as sensitivity analyses for important outcomes and will address the effect of the intervention in those who receive it and provide follow-up data.

The significance level used throughout will be 0.05, and 95% confidence intervals will be reported. The primary conclusion of the trial will be based on the results from the primary analysis of the primary outcome, and all secondary analyses will be considered as being supportive of the primary results.

All analyses will be carried out using appropriate, validated statistical software such as Stata [17] or R [18]. The relevant package and version number used for the analysis will be recorded and reported.

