#### Compliance

Attendance will be recorded for the intervention, and compliance with the test intervention will be defined as fulfilling at least four treatment sessions. This is the clinical consensus definition based on variation in current practice and expected effective dose. In addition, this represents participants who have received at least half of the specified intervention.

For primary and key secondary outcomes, a complier average causal effect (CACE) analysis will be estimated using an instrumental variable approach to assess the impact of compliance on the outcomes [20, 21]. This will be a sensitivity analysis for these outcomes, and it will provide an unbiased estimate of treatment effect amongst those who would receive the intervention as planned.

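### The per-protocol set mixes an as-treated grouping with a per-protocol exclusion, leaves receipt of treatment undefined, and so gives an estimate that randomisation does not protect

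*SAP article*

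**What the plan says.** All of this is in the SAP article.

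- **General analysis principles, grouping.** "The PP population will be analysed according to the intervention they actually received".
- **General analysis principles, exclusion.** Major deviators are specified as "those who did not receive treatment or did not provide any follow-up data, will be excluded from the PP population".
- **General analysis principles, timing.** The definition is to be "finalised by the trial statistician during a blinded analysis of the data (i.e. without details of treatment allocation"; in the same step, "any unanticipated protocol deviations which occur will be identified at this point".
- **General analysis principles, status and target.** "Analysis of the PP population will be conducted as sensitivity analyses for important outcomes", and the analysis "will address the effect of the intervention in those who receive it and provide follow-up data". ITT is the primary set, and the trial's conclusion rests on the primary analysis.
- **Compliance.** "Attendance will be recorded for the intervention, and compliance with the test intervention will be defined as fulfilling at least four treatment sessions". This definition serves an instrumental-variable CACE analysis of the primary and key secondary outcomes.
- **Analysis of primary outcome** (last sentence) and **Analysis of secondary outcomes.** The PP analysis is used to test how robust the conclusions are, for the primary outcome and for the key secondary outcomes (LLFDI frequency and limitation, OKS, KOOS).

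**The concern.** Two different rules are joined in one analysis set. Grouping by treatment received is an as-treated rule. Removing people who were not treated is a per-protocol rule. An intervention participant who had none of the programme but had ordinary physiotherapy fits both: dropped as untreated, or counted as usual care. The two readings give different estimates and the SAP does not choose. It also does not say what it would mean for a usual-care participant not to have received treatment, so the exclusion could fall on one arm or on both.

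Under either reading, membership or grouping depends on what happened after randomisation: whether treatment was taken up, which treatment it was, and whether follow-up was given. If those who take up treatment differ in prognosis from those who do not, the comparison mixes that difference with the treatment effect. No adjustment for predictors of receipt is specified. The Background notes that current rehabilitation particularly fails people who are frail, isolated or without transport, so it would be unsafe to assume that receipt is unrelated to prognosis.

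At stake is how the sensitivity analyses are read. A PP result that agrees with ITT could be taken as confirmation, and one that disagrees as doubt, when either could reflect selection.

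A smaller point concerns blinding. Identifying deviations from data on treatment received may reveal the arm, and the SAP does not say how this is avoided.

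**Working it through.** **1. Design benchmark.** The section Sample size gives a standardised effect of 0.275, illustrated as 3 points with an SD of 10.91, 90% power, 5% two-sided significance and 10% loss.

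- 3 / 10.91 = 0.275.
- The normal approximation gives 278 per arm, 556 in total; 556 / 0.9 = 618.
- The t-based calculation gives 279 per arm (power 0.9002); 279 / 0.9 = 310 per arm, 620 in total.

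The stated 620 is reproduced and is not in dispute. Only the 3 points, the 0.275 and the SD are used below.

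**2. The two rules side by side.**

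| Participant | Grouping by treatment received | Exclusion of the untreated |
|---|---|---|
| Intervention arm, never had the programme, had ordinary physiotherapy | Counted as usual care | Dropped, if treatment means the allocated programme |
| Usual care, had no rehabilitation | No group to join | Dropped only if receipt is defined for usual care, which it is not |

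**3. Possible size of the bias.** The following assumptions are not in the documents: the true effect is zero; a share q of the intervention arm is never treated; their mean outcome lies g SD below that of the treated in the same arm; allocation is 1:1; nobody is removed from usual care. The primary model adjusts for baseline score and site, so g should be read as the gap that remains after that adjustment.

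Set the overall mean of each randomised arm to 0. The treated in the intervention arm then have mean +qg and the never-treated have mean −(1 − q)g.

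- *Excluded from the intervention arm only:* bias = qg − 0 = qg.
- *Moved to usual care instead:* the enlarged group has mean −q(1 − q)g / (1 + q), so bias = qg + q(1 − q)g / (1 + q) = 2qg / (1 + q).

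Points are SD units times 10.91. Shares are of the design effect of 0.275.

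| q | g (SD) | Excluded: points (share) | Moved: points (share) |
|---|---|---|---|
| 5% | 0.25 | 0.14 (5%) | 0.26 (9%) |
| 5% | 0.5 | 0.27 (9%) | 0.52 (17%) |
| 10% | 0.25 | 0.27 (9%) | 0.50 (17%) |
| 10% | 0.5 | 0.55 (18%) | 0.99 (33%) |
| 20% | 0.25 | 0.55 (18%) | 0.91 (30%) |
| 20% | 0.5 | 1.09 (36%) | 1.82 (61%) |

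Check of the last row: 0.20 × 0.5 = 0.10 SD, and 0.10 × 10.91 = 1.09 points. For moving, 2 × 0.10 / 1.20 = 0.167 SD, and 0.167 × 10.91 = 1.82 points.

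The two columns are alternatives. A participant is either dropped or moved, so the figures must not be added.

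**The case against.** The strongest reply is that the consequence is contained. ITT is primary and carries the conclusion, PP is labelled a sensitivity analysis, and an instrumental-variable CACE is already planned for the same outcomes. This stands, and it limits the point to how the sensitivity analyses are defined and read. It does not remove the ambiguity in the rule or the claim made for its result.

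A second reply is that the size is assumed. This also stands. The documents give no rate of non-receipt, no crossover rate and no gap in outcome. The lowest case, 0.14 point, is negligible.

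A reader might also infer more than the text supports:

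- *That PP exclusion rests on attendance recorded in one arm only.* The exclusion rule mentions neither attendance nor an arm. Attendance and the four-session threshold appear under Compliance and serve CACE. That section says attendance is recorded for the intervention, not that it is recorded nowhere else.
- *That the PP set cannot be finalised blind.* What is finalised blind is the definition, and a rule can be written without knowing allocation. Only the narrower risk remains, that reviewing deviations may reveal the arm.
- *That PP and CACE contradict each other because someone with one session might be kept in PP yet be a CACE non-complier.* PP has no session threshold and its definition is still open. The two analyses also state different targets, so a difference between them is not in itself an error.

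**Conclusion.** The point holds as a defect in a sensitivity analysis. As written, the PP rule is ambiguous for a never-treated intervention participant, undefined for usual care, and selective on post-randomisation events under any reading. Its result should not be presented as the effect in those who receive the intervention, or as a clean check on robustness.

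Under the stated assumptions the bias would be about 0.14 to 1.09 LLFDI points if the never-treated are excluded from one arm, or about 0.26 to 1.82 points if they are moved to usual care, against a 3-point design difference. These figures show what the rule could do; they do not predict what it will do in this trial. If non-receivers were also removed from usual care, the exclusion bias could shrink or change sign. If the never-treated had the better prognosis, both biases would reverse. The ITT primary analysis and the conclusion drawn from it are unaffected.

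**What to change.** 1. Delete the regrouping by intervention received, and analyse everyone in the PP set in the arm to which they were randomised.
2. Define receipt of treatment for both arms before unblinding, and state who is excluded in each. State also how deviations will be reviewed without revealing allocation, or that this step is not blind.
3. Make the planned instrumental-variable CACE the main treatment-received analysis for the primary and key secondary outcomes. It keeps the randomised comparison, but it needs its own assumptions, chiefly that the offer of the programme acts on outcome only through compliance as defined. These should be stated.
4. If a PP analysis is kept, adjust it for baseline predictors of receipt, and label it non-randomised and exploratory wherever it is reported.

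The cost is SAP wording, since CACE is already planned and, according to Trial status, follow-up was still under way. The small downside is that a conventional PP table carries less weight.

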#### Descriptive analyses

The flow of participants through the trial, including the number of individuals assessed, recruited, randomly assigned to either usual care or multi-component community-based rehabilitation, and analysed for the primary outcome will be summarised using a Consolidated Standards of Reporting Trials patient reported outcome (CONSORT-PRO) extension flow chart [19] (see Fig. 1).

**Fig. 1 Fig1:**
[figure not shown]
CONSORT flow chart of trial participants

The baseline comparability of the two randomised groups in terms of: (1) risk factors for poor outcome after knee replacement according to the CORKA screening tool [10]: (2) baseline characteristics (Table 1); and, (3) primary and secondary outcomes at baseline will be presented. Numbers with percentages will be used to describe binary and categorical variables, and either means and standard deviations or medians and interquartile ranges, if a variable is not normally distributed, will be used for continuous variables. There will be no tests of statistical significance or confidence intervals for differences between randomised groups.

**Table 1 Tab1:** Baseline characteristics

Baseline characteristic	Type	Levels or scale
Gender	Categorical	Male; Female
Age	Categorical	55–64 years; 65–74 years; 75 years or more
Age	Continuous	Years
Fallen in the last year	Categorical	Yes; No
Number of falls in last year	Continuous	NA
Previous lower limb surgery	Categorical	Yes; No
Charnley ABC classification	Categorical	Single knee arthroplasty; Both knees affected; Multiple joint disease (or other disability)
Self-reported current mobility (stairs)	Categorical	Normal; One step at a time; Down with rail; Up and down with rail; Unable down; Unable
Self-reported current mobility (support)	Categorical	None; Stick outdoors; Stick always; 2 sticks; 2 crutches; Walking frame
Body mass index	Continuous	kg/m^2^

#### Loss to follow-up, withdrawals, and missing data

Losses to follow-up and withdrawals before the 6 months follow-up and the 12 months follow-up will be reported by intervention arm, together with reasons for the losses. To ensure that there are no differential losses between the two groups, this will be tested using absolute risk differences and a chi-squared test. The patterns of availability of data will be presented by treatment arm and overall for all outcomes from baseline to the end of follow-up. Where appropriate, differentiation will be made between partially completed and fully missing outcome data. Reasons for missing data will also be summarised.

#### Compliance

Attendance will be recorded for the intervention, and compliance with the test intervention will be defined as fulfilling at least four treatment sessions. This is the clinical consensus definition based on variation in current practice and expected effective dose. In addition, this represents participants who have received at least half of the specified intervention.

For primary and key secondary outcomes, a complier average causal effect (CACE) analysis will be estimated using an instrumental variable approach to assess the impact of compliance on the outcomes [20, 21]. This will be a sensitivity analysis for these outcomes, and it will provide an unbiased estimate of treatment effect amongst those who would receive the intervention as planned.

